### SC

The control comparator is standard CBT care delivered within IAPT services prior to CBT-ts training. CBT is delivered as part of range of interventions offered at step 3 within the NICE stepped care model. CBT treatment protocols are delivered in accordance with NICE guidance for people with CMD. Treatment duration varies according to presenting problem and minimum dose necessary to achieve recovery, but NICE recommends individuals should receive up to 20 weekly sessions unless they recover beforehand (https://www.nice.org.uk/guidance/cg123/chapter/1-guidance).

### Outcomes

A summary of study outcomes is shown in table 3, and schedules of outcome measures for service users and therapists are provided in tables 2 and 4.

**Table 3 T3:** Summary of study outcomes

Category	Measure	Primary/secondary	Details
Service user recovery	IAPT-defined ‘Recovery’	Primary	The primary outcome is the proportion of IAPT service users with CAPE-P15 score of 1.47 or above who have recovered by the end of treatment. Recovery is a national IAPT programme performance metric, with an individual deemed recovered if they scored above the clinical cut-off on the PHQ-9^35^ and/or GAD-7^36^ before treatment, ie, 10 and 8, respectively, and below the clinical cut-off at the end of treatment on both measures.^37^ If recorded, an anxiety disorder specific measure is used in place of the GAD-7 if that is the focus of treatment.^38^
	IAPT-defined ‘Recovery’	Secondary	As for the primary outcome, but for IAPT service-users reaching the lower threshold score for CMD-PE (CAPE-P15 score of 1.30 and above).^39^
	IAPT-defined ‘Reliable Improvement’	Secondary	Service users are considered reliably improved if they show any improvement in scores on the appropriate outcome measures between pre and post treatment, that exceeds the measurement error of the scales.^38^
	IAPT-defined ‘Reliable Recovery’	Secondary	Service users are considered reliably recovered if they meet both criteria for Reliable Improvement and for Recovery.^38^
Health economic measures	Modified adult service use schedule for early intervention (EI-ADSUS)	Secondary	Individual-level resource use will be measured using a modified version of EI-ADSUS. This was developed in previous research with similar populations^37^ and adapted for electronic participant self-completion. It will include all-cause hospital and community-based health and social care resource use as well as information on time off work due to mental health.
	EuroQol measure of health-related quality of life three level (EQ-5D-3L)	Secondary	Health-related quality of life will be measured using the EQ-5D-3L, a generic, preference-based measure based on five dimensions (mobility, self-care, usual activities, pain/discomfort and anxiety/depression). Each dimension is rated on three levels (no problems, some problems and severe problems).^40^
	EuroQol measure of health-related quality of life five level (EQ-5D-5L)	Secondary	The EQ-5D-5L is also a health-related quality of life measure based on five dimensions (mobility, self-care, usual activities, pain/discomfort and anxiety/depression), but each dimension is rated on five levels (no problems, slight problems, moderate problems, severe problems and extreme problems.^41^ It has been demonstrated that the EQ-5D-3L is a useful, valid instrument in young people with emerging psychotic symptoms.^42^ However, the new five-level version, may prove more sensitive to change and is now recommended for economic evaluation by National Institute for Health and Care Excellence^43^ but has not been validated in this population. Therefore, we will test the sensitivity of the EQ-5D-5L in comparison to the EQ-5D-3L.
Therapist adherence	Supervision checklist	Secondary	Therapist adherence measured using a supervision checklist and adherence score completed during the 6 monthly supervision sessions held after CBT training. Trial supervisors will review and collate therapy session notes and rate adherence to the CBT-ts approach.

CAPE-P15, Community Assessment of Psychic Experiences—Positive 15-items Scale; CBT, cognitive behavioural therapy; CBT-ts, CBT tailoring for severity; CMD-PE, common mental disorder psychotic experiences; GAD-7, General Anxiety Disorder Assessment-7; IAPT, improving access to psychological therapies; PHQ-9, Patient Health Questionnaire-9.

**Table 4 T4:** Schedule of IAPT therapist enrolment, interventions and assessments

	Trial set-up	Randomisation	Control condition	Intervention condition
Identification				
IAPT teams and potential therapists identified and grouped to form clusters	x			
Enrolment and randomisation				
Informed consent	x			
Clusters randomised		x		
Intervention				
CBT-ts training				x
CBT-ts supervision				x
Assessments				
Adherence and engagement record				x

CBT-ts, cognitive behavioural therapy-tailoring for severity; IAPT, improving access to psychological therapies.

### Process evaluation

The aim of the process evaluation is to assess the views of all stakeholders involved in the experience and delivery of the TYPPEX swcRCT and CBT-ts, and to investigate the implementation of CBT-ts as designed, including any influences on uptake, delivery and fidelity. An overview of the key themes explored with each stakeholder group is given in table 5.

**Table 5 T5:** Key themes explored in the process evaluation for each stakeholder group

Stakeholder group	Key themes
Service users	Experiences of treatment and therapist. Views on improving IAPT services. Views on CBT-ts.
Therapist	Design and goals of CBT-ts. Experience of the CBT-ts training. Experience of delivery and fidelity.
Line managers	Design and goals of CBT-ts. Experience of the CBT-ts training. Experience of delivery and fidelity at the therapist-service user level. Experience of delivery and fidelity at the IAPT service level.
Study team and collaborators	Rationale for CBT-ts. Implementation and components. Outcomes and measurement. Modifications and changes to CBT-ts.
Senior National Health Service managers/commissioners	Relevance of CBT-ts in IAPT. Implementation of CBT-ts model. Negotiating change. Measuring success.

CBT-ts, cognitive behavioural therapy-tailoring for severity; IAPT, improving access to psychological therapies.

The aim of sampling for the process evaluation will be to achieve theoretical saturation,^21^ where further new data are unlikely to achieve further insights or to add to analytic depth. Up to 32 service users across the eight clusters with scores of 1.47 and above on the CAPE-P15 and who have completed at least two CBT treatment sessions with a CBT-ts trained therapist will be recruited including those who have completed treatment, those who are still undergoing therapy and those who dropped out of treatment. Where possible, purposive sampling will be used to ensure diversity of gender and ethnicity and exposure to number of sessions of therapy.

Between 16 and 24 IAPT therapists (with a minimum of two per cluster) who completed CBT-ts training and subsequently delivered at least three treatment sessions to a minimum of two service-users scoring 1.47 and above on the CAPE-P15 will be recruited. Additionally, we will conduct 18–25 interviews with IAPT clinical supervisors/managers from participating IAPT teams who line manage or supervise a CBT-ts trained therapist, senior non-clinical NHS managers with responsibility for delivery of IAPT services at Trust level or responsibility for commissioning IAPT services, and members of the trial team and collaborators who contributed to the design, development or implementation of TYPPEX. In all cases, purposive sampling will be used to ensure representation of a wide range of perspectives and experiences.

### Data management

Pseudonymised outcome data will be received by Norwich Clinical Trials Unit from sites and uploaded to a central study database stored on servers based at the University of East Anglia. Health economic questionnaire data will be collected using Research Electronic Data Capture (REDCap) software (https://www.project-redcap.org). Questionnaires will be completed online or by post by service users. Pseudonymised clinical data will be linked to consented participants’ health economics data held by the Norwich Clinical Trials Unit (NCTU).

Data collection will include retrospectively recorded IAPT data from 23 March 2020 until trial start. This data, covering the period of UK lockdown during the COVID-19 pandemic, will provide information on the nature of IAPT service provision during this time, and any changes in baseline morbidity. The aim of the data collection is to provide insight into standard of care and baseline severity during the pandemic, to assist decision-making by the trial oversight committees.

Data will be handled in accordance with a data management plan and comply with the principles of the International Conference on Harmonisation Good Clinical Practice, within the Standard Operating Procedures for Data Management in NCTU and where appropriate with the University of East Anglia Information Technology (UEA IT) procedures. Interview transcriptions will be anonymised in adherence with the ‘Guidance on Anonymisation’ issued by the UK Data Service (https://www.ukdataservice.ac.uk/manage-data/legal-ethical/anonymisation.aspx). Anonymised data will be stored in password-protected files on the firewall-protected University of Cambridge servers.

### Statistical analyses

The primary analysis will compare IAPT-defined recovery of service users with CMD-PE as determined by the CAPE-P15 cut-off of 1.47 in the control phase with those in the intervention phase (post-training). Recovery proportions and means will be compared at individual therapist and team level after adjusting for the stepped-wedge cluster design. Adjustment will also be made for the baseline characteristics and other covariates. Time will be included as a set of indicator variables.

Analyses of clinical effectiveness will be based on the intention-to-treat (ITT) population with all available follow-up data from all new service users with CMD-PE on the caseload of participating therapists, controlling for baseline scores on depression and anxiety disorder specific measures. The primary ITT analysis is intended to provide inferences regarding the effectiveness of the intervention overall. It does not provide inferences regarding the causal effect of the intervention itself, but on the intervention as deployed in ‘real life’, therefore compliance information is not necessary to ensure that the ITT analysis is valid. As soon as a therapist has their first session of CBT-ts training, they begin to practise differently, so this date will mark the beginning of their intervention phase.

A logistic mixed effects regression model will be used for the primary outcome analysis. The cluster effect by both the therapist team and therapist will be considered in the multilevel analysis. Adjustment for potential prognostic variables will be agreed prior to analysis between the trial statisticians and the chief investigator.

Intracluster correlation coefficients and 95% CIs will be reported for the primary and secondary outcomes. All analyses will be two-tailed and at the 5% level of significance.

Summary statistics of baseline characteristics at the cluster and the individual level will be reported where appropriate. Analyses will be conducted in Stata or R. Publication of results will include a participants/cluster flow diagram, and results will be reported according to the Consolidated Standards of Reporting Trials statement for stepped wedge designs.

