### Trial design and participants

The TYPPEX study is a pragmatic, multicentre swcRCT with nested health economic and process evaluations. It involves eight NICE step-3 IAPT teams (clusters) of CBT therapists across three mental health trusts in England: Cambridgeshire and Peterborough NHS Foundation Trust, Norfolk and Suffolk NHS Foundation Trust and Sussex Partnership NHS Foundation Trust. Each trust (organisational unit within the National Health Services of England and Wales) serves a mixed urban and rural population with a wide socioeconomic range, including some high levels of deprivation, covering a total population of approximately 2.8 million.

Clusters will be randomised to different sequences rather than, strictly speaking, different arms. The sequences dictate the order in which each cluster switches from the control to intervention condition. TYPPEX swcRCT has five measurement periods and four steps, with two clusters switching to the intervention condition at each step. As the intervention is cluster randomised at the level of IAPT team, and the delivery of therapy by these teams may be subject to regional variation, each cluster will act as its own internal control. All clusters will start in the control condition and move to the intervention condition (see figure 1).

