### Randomisation

IAPT therapists from local teams within participating sites will be recruited and grouped as study clusters before randomisation (without stratification by cluster characteristics) to the control-intervention sequences via computer written code. In most cases, clusters will be formed from a single IAPT team. Some teams may have fewer IAPT CBT therapists available for training due to empty therapist posts or service demands. In these cases, two local IAPT teams will be merged to create a cluster. Once clusters are allocated, IAPT service managers will be approached and CBT-ts training courses arranged in line with each cluster randomisation point.

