### Sample size

CBT-ts training will be delivered to step-3 CBT therapists in eight clusters, randomised at four steps. In each cluster, approximately 7–10 therapists will receive training, with the intention for at least five therapists to deliver therapy throughout each cluster period, to allow for inevitable therapist turnover and sickness.

Based on our prevalence studies of CMD-PE in IAPT^5 10^ and considering average caseloads of 15–20 services users per therapist over 6 months, each therapist will deliver therapy to a minimum of three people. Pragmatically, the total number of eligible service users receiving therapy from a participating therapist during the whole trial may be higher, but only control service users who complete therapy during their cluster’s control phase and intervention service users who complete therapy prior to the end of the intervention phase, will be included in the primary outcome analysis. Based on results from our previous TYPPEX feasibility work, we expect that 6-month steps would be sufficient for this.

All service users will be identified as having PE with the CAPE-P15 score threshold of 1.47^19^ for both frequency of and distress associated to psychotic experiences at baseline, resulting in a minimum of 15 service users per cluster period. Eight clusters and four randomisation steps result in 20 control condition cluster periods and 20 intervention condition cluster periods. Three hundred IAPT service users will be recruited during the control condition and 300 during the intervention condition across all sites. In addition to the number of clusters and the steps presented above, we have assumed: an intracluster correlation coefficient of 0.05, a significance level of 0.05 and an improvement in recovery from 0.39 (control) to 0.58 (intervention).^5 10^ Based on these assumptions, the proposed sample size will allow us to detect such a difference with just over 80% power. Although this ignores that clustering also happens at the therapist level, it has been shown that ignoring an additional, lower level of clustering is a conservative estimate of the power. This is not sensitive to the choice of intracluster correlation coefficient.^20^

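### The intervention phase starts at each therapist's own first training session, not at the cluster's randomised switch, so exposure in the analysis labelled ITT depends on attendance

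*Protocol article*

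**What the plan says.** The Trial design and participants section randomises clusters (IAPT teams) to sequences: "The sequences dictate the order in which each cluster switches from the control to intervention condition". There are eight clusters, five periods and four steps, with two clusters switching at each step.

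The Sample size section keeps to that level. It counts 20 control and 20 intervention cluster periods, and a control service user enters the primary analysis only if therapy is completed within the control phase of that user's cluster.

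The Randomisation section ties training to the step loosely: "CBT-ts training courses arranged in line with each cluster randomisation point". The article gives no fixed date or permitted window.

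The Statistical analyses section states the population: "Analyses of clinical effectiveness will be based on the intention-to-treat (ITT) population with all available follow-up data from all new service users with CMD-PE" on participating therapists' caseloads. It adds that "compliance information is not necessary to ensure that the ITT analysis is valid". It then sets the start of exposure therapist by therapist: "As soon as a therapist has their first session of CBT-ts training, they begin to practise differently, so this date will mark the beginning" of that therapist's intervention phase. No analysis by randomised switch date is mentioned.

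**The concern.** Randomisation fixes when a cluster switches. When a given therapist first attends training is an event after randomisation, in a trial where therapists and research team are unblinded. If that event sets the exposure code, users of a late-trained therapist move from the intervention group to the control group because of something the therapist did or could not do. Reasons for lateness, such as workload or sickness, may be related to outcome.

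The paragraph is also at odds with itself. It says that compliance information is not needed and then uses attendance to assign phase. It wants the effect as deployed in real life, yet late deployment is taken out of the intervention group and added to control.

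At stake is whether the headline comparison keeps the protection of randomisation around each switch.

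**Working it through.** **1. The definitions side by side.** Take a service user who starts therapy after the cluster's randomised switch, with a participating therapist who has not yet had a first session.
- Trial design and participants: the cluster has switched, so the user belongs to the intervention condition.
- Sample size: the user cannot complete therapy within the cluster's control phase, so cannot be counted as a control.
- Statistical analyses: the therapist's intervention phase has not begun, so the user is a control.

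These cannot all hold.

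**2. The plan's own figure.** The stated power is just over 80%. Inputs from Sample size: 8 clusters (I), 5 periods (T), 15 users per cluster period, ICC 0.05, recovery 0.39 against 0.58, two-sided 5%.
- Total variance: (0.39×0.61 + 0.58×0.42)/2 = 0.24075.
- Between clusters: τ² = 0.05×0.24075 = 0.01204. Cluster-period mean: σ² = 0.95×0.24075/15 = 0.01525.
- Hussey–Hughes: Var = Iσ²(σ² + Tτ²) / [(IU − W)σ² + (U² + ITU − TW − IV)τ²], with U = 20, W = 120, V = 60.
- Var = 0.009202/2.0544 = 0.004479, so SE = 0.0669.
- Power = Φ(0.19/0.0669 − 1.96) = Φ(0.88) = 81.0%.

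The figure reproduces. It assumes a clean cluster-level switch, which the therapist-date rule does not guarantee.

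**3. Size of the bias.** Expected value of a generalised least squares estimate on the risk-difference scale, with time indicators and random team and therapist effects: (X′V⁻¹X)⁻¹X′V⁻¹E[y].
- From the article: 8 clusters, six-month steps, 5 delivering therapists per cluster, 3 users per therapist per step (0.5 per month), team ICC 0.05.
- Assumed: 1 of 5 therapists per cluster is trained late, with recovery 10 points below the others throughout; therapist ICC between 0.05 and 0.

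Results in percentage points; ranges run from therapist ICC 0.05 to 0:

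| Delay | No effect, first-training date | No effect, randomised date | True 19 points, first-training date | True 19 points, randomised date |
|---|---|---|---|---|
| 1 month | +0.3 to +0.6 | 0.0 | 19.3 to 19.6 | 18.4 |
| 2 months | +0.7 to +1.2 | 0.0 | 19.7 to 20.2 | 17.9 |
| 6 months | +2.0 to +3.4 | 0.0 | 21.0 to 22.4 | 15.6 to 15.7 |

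If the late therapists do 10 points better, the no-effect biases change sign: −2.0 to −3.4 at six months.

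**4. What the model can absorb.** With fixed therapist effects, the bias from a constant therapist difference is 0.0. Random therapist effects shrink it without removing it, as the table shows. Neither handles a difference that changes over time, or selection of which users start before or after the training date.

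**5. Price of randomised-date coding.** The step 2 formula with the diluted effects (SE about 0.0670) gives Φ(0.184/0.0670 − 1.96) ≈ 78% for a one-month delay and Φ(0.179/0.0670 − 1.96) ≈ 76% for two months, against 81.0% with no delay.

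**The case against.** A reader might infer more than the text supports: that therapists who never attend, or who join the team later, stay in the control group indefinitely, so that the whole ITT analysis is an as-treated comparison. With 1 of 5 never trained and the same 10-point deficit, that reading would give a spurious +3.9 to +6.0 points. The article does not say this. It states when a therapist's intervention phase begins and is silent on those who never begin. Participating therapists must be willing and able to consent to training and are recruited before randomisation, and nothing says that later joiners become participants. The phrase "to allow for inevitable therapist turnover and sickness" explains why about 7–10 therapists are trained so that at least five deliver therapy. It describes a precaution and is no evidence that delivering therapists go untrained.

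Other points also limit the concern, and they stand. CBT-ts is described as a team-level intervention, with courses arranged around the randomisation point, so delays may be short. Making the first of three modules the start, and not completion, brings partly trained therapists into the intervention phase, which leans towards ITT. The planned analysis considers therapist effects and adjusts for baseline depression and anxiety scores. The late share, the 10-point gap and the delays are all assumed.

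It could also be said that late and replacement therapists are a matter for the statistical analysis plan. That would answer a missing detail. Here the article states a rule for the start of exposure, and a plan that follows the article would inherit it.

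**Conclusion.** The point holds as a conflict between a stated analysis rule and the cluster-level randomisation, phase definition and ITT label. For any therapist trained after the cluster's switch, the rule makes exposure depend on attendance and so opens the primary comparison to bias in either direction.

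The article does not allow the size to be determined. Under the stated assumptions the bias is small against 19 points if delays are a month or two (0.3 to 1.2 points), and no longer negligible if they reach a full step (2.0 to 3.4 points). A constant therapist difference would vanish with fixed therapist effects, but the article says only that therapist clustering will be considered. To say that randomisation's protection is lost altogether would go too far. This should be fixed; it does not invalidate the design.

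**What to change.** In the primary ITT analysis, code every eligible service user of participating therapists by the cluster's randomised switch date, whether or when the therapist was trained. Keep the first-training date for a sensitivity analysis labelled as-treated. Report the gap between scheduled and actual training dates by cluster and therapist. Make the phase definitions in Trial design and participants, Sample size and Statistical analyses agree.

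This is a change of wording and coding, with no new data beyond the training dates that the present rule already needs. The cost is dilution and some power when training is late: in the example, about 18 points in place of 19, and about 76–78% power in place of 81%, for a one- to two-month delay in 1 of 5 therapists. That diluted figure is the real-life effect the plan says it wants to estimate.

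### The stated power, and the error rate of the primary model as named, depend on a team effect that stays constant over 30 months; with eight clusters a small-sample method is also needed

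*Protocol article*

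**What the plan says.** **Design** (Protocol article, Trial design and participants; Sample size). "TYPPEX swcRCT has five measurement periods and four steps, with two clusters switching to the intervention condition at each step". The sample-size section counts the cells: "Eight clusters and four randomisation steps result in 20 control condition cluster periods and 20 intervention condition cluster periods", with the caseload assumption "resulting in a minimum of 15 service users per cluster period". On period length, "we expect that 6-month steps would be sufficient for this". Five 6-month periods make 30 months, which matches the recruitment window of March 2021 to September 2023 under Trial status.

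**Power** (Sample size). With ICC 0.05, a 5% significance level and recovery of 0.39 against 0.58, the article concludes that "the proposed sample size will allow us to detect such a difference with just over 80% power". After a remark on therapist-level clustering it adds: "This is not sensitive to the choice of intracluster correlation coefficient". It gives no value for how the correlation within a team changes between periods.

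**Analysis** (Statistical analyses). The primary outcome is analysed by a logistic mixed model, with time entered as indicator variables. On the random part: "The cluster effect by both the therapist team and therapist will be considered in the multilevel analysis". On testing: "All analyses will be two-tailed and at the 5% level of significance". No team-by-period effect, reference distribution or small-sample correction is named, and none is ruled out.

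**The concern.** A random intercept for team, and one for therapist, treats two patients of the same team as equally correlated whether they were seen in the same period or two years apart. Period indicators remove changes that all teams share. They cannot remove changes specific to one team, such as local staffing, caseload mix or local recovery from the pandemic. The article itself expects therapist turnover and regional variation in delivery.

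In a stepped wedge, much of the treatment contrast is within team, before against after. If teams drift and the model has no term for it, the drift is counted as precise information about the intervention and the standard error is too small. Separately, with eight clusters the normal approximation for a Wald statistic is itself too optimistic. At stake are the error rate of the primary test, the width of its confidence interval, and whether the published power claim describes the trial.

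**Working it through.** **1. Inputs.** From the article: 8 teams, 5 periods, 2 teams crossing per step, m = 15 per cell, ICC ρ = 0.05, p0 = 0.39, p1 = 0.58, two-sided α = 0.05. Assumed, because the article gives no value: the cluster autocorrelation r, which is the correlation of a team's effect between two periods.

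**2. Formula.** Hussey-Hughes generalised least squares on cell means, with fixed periods:

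- total variance σ² = mean of 0.39×0.61 and 0.58×0.42 = (0.2379 + 0.2436)/2 = 0.24075
- team variance τ² = ρσ²; sampling variance of a cell mean = (1−ρ)σ²/15
- covariance of two cells of one team = rτ²; variance of a cell = τ² + (1−ρ)σ²/15
- power ≈ Φ(0.19/SE − 1.96)

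**3. Reproducing the plan's figure.** With ρ = 0.05 and r = 1: τ² = 0.01204, sampling variance = 0.95×0.24075/15 = 0.01525, SE = 0.0669, 0.19/0.0669 = 2.84, power 81.0%. Taking the total variance at the pooled or control proportion instead gives 79.6% or 81.5%. The stated figure is therefore the calculation with a constant team effect.

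**4. Relaxing the constant team effect** (normal test, 15 per cell):

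| ICC | r = 1 | r = 0.8 | r = 0.5 |
|---|---|---|---|
| 0.02 | 83.9% | 83.0% | 82.4% |
| 0.05 | 81.0% | 76.7% | 72.2% |
| 0.10 | 80.9% | 70.5% | 60.2% |
| 0.15 | 82.2% | 66.0% | 51.7% |

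The first column is nearly flat, so the insensitivity sentence is about right at r = 1. In the other columns power falls steadily as the ICC rises. If the correlation instead decays by a factor of 0.8 per period, power at ICC 0.05 is 72.7% (pooled-proportion variance, from a base of 79.6%).

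**5. Type I error of the named model with an uncorrected Wald z test.** Null simulations with period indicators and team variance matched to ICC of about 0.05. Layouts with therapists have 5 per team and 3 users each per period, with no turnover:

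| Simulated model | r = 1 | r = 0.8 | r = 0.5 |
|---|---|---|---|
| Logistic, team + therapist (therapist variance 0.10 on the logit scale, 2,000 runs) | 6.3% | 8.2% | 9.6% |
| Logistic, team + therapist (therapist variance 0.08, 4,000 runs) | 7.0% | 7.5% | 10.6% |
| Logistic, team only (10,000 runs) | 6.3% | 7.6% | 9.6% |

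A linear approximation with a team effect only gave about 7%, 8.5% and 10%.

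**6. The reference distribution matters.** For the team-only logistic model, the same statistics referred to t on 34 df reject in 5.3%, 6.6% and 8.5% of runs (r = 1, 0.8, 0.5). Referred to t on 6 df, the logistic models reject in 1.8% to 3.8%. A cell-mean analysis with fixed team and period effects and t on 40 − 13 = 27 df held 4.9-5.2% in 20,000 runs per scenario.

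**7. Power of that cell-mean analysis.** After removing team and period effects, the treatment indicator has a residual sum of squares of 3, so SE = √{[(1−r)τ² + (1−ρ)σ²/15]/3}:

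- ρ = 0.05, r = 1: √(0.01525/3) = 0.0713, power 73%
- ρ = 0.05, r = 0.8: √(0.01766/3) = 0.0767, power 67%
- ρ = 0.10, r = 0.8: √(0.01926/3) = 0.0801, power 63%

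**The case against.** **The article does not fix the test.** A reader might infer that the primary model contains only team and therapist effects and that its false-positive rate is above 5%. The text does not support that. It says these effects are to be considered, gives a significance level but no reference distribution, and excludes neither a team-by-period effect nor a correction. Such details are commonly left to the SAP, which is not shown. With t on 6 df the simulated error is below 5%, so even the direction depends on an unstated choice. This stands: the type I error figures apply only if an uncorrected Wald z test is used.

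**The power figure is right on its own terms.** It reproduces, and the insensitivity sentence is about the ICC, not the autocorrelation. It may even refer to the remark on therapist-level clustering just before it. This stands in part. The arithmetic is sound, but a reader will take the two sentences as a claim of robustness, and that claim rests on an assumption that is not disclosed.

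**Decay is assumed.** Common pandemic effects go into the period indicators, and turnover is partly carried by the therapist effect. That is fair. Team-specific drift over 30 months is plausible, but its size is unknown.

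**There may be margin.** It is tempting to call the stated power a best case. The article does not support that: 15 per cell is given as a minimum. At ICC 0.05, 18 per cell gives 87% (r = 1) or 82% (r = 0.8), and 20 per cell gives 90% or 85%. An ICC of 0.02 also keeps power at 82% or more. The margin is not guaranteed, because only users who complete therapy within the phase enter the primary analysis.

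**Conclusion.** The point holds in conditional form.

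- **Power.** Just over 80%, and its insensitivity to the ICC, hold only for a team effect that is constant over five 6-month periods. With 15 users per cell and a normal test, power is 81%, 77% and 72% at autocorrelation 1, 0.8 and 0.5 (ICC 0.05), and about 71% at ICC 0.10 with autocorrelation 0.8.
- **Type I error.** If the model as named were tested with an uncorrected Wald z test, the error would be about 6-7% with a constant team effect and about 7.5-10% at autocorrelation 0.8 to 0.5. It is not established that the trial will use that test.

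The autocorrelations, the therapist variance and the absence of turnover in the simulations are assumptions; the ICC of 0.05 is the protocol's. This should be settled before analysis. It does not show that the design is invalid.

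**What to change.** 1. Add a team-by-period random effect to the primary model, beside team and therapist.
2. Pre-specify a small-sample method for the primary p-value and confidence interval. A permutation test suits this design: allocation is unstratified, so the 8!/(2!)⁴ = 2,520 assignments of eight clusters to four sequences are the natural reference set. A cell-mean analysis with t on 27 df is an alternative that holds its level but has less power.
3. Limit the insensitivity sentence to a time-constant cluster effect.
4. Restate power as a range over stated autocorrelation values, computed for the method actually chosen. Under a normal test the range is about 70-81% (ICC 0.05-0.10, autocorrelation 0.8-1). A small-sample correction lowers it, for example to 63-73% for the fixed-effect cell-mean t analysis. The normal-test range should not be printed beside a corrected analysis.

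If the SAP already contains items 1 and 2, only the sample-size wording needs changing. The cost is SAP text and modest programming, somewhat wider intervals and a less favourable quoted power. No extra participants are needed.
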